**Fig. 3 Fig3:**
[figure not shown]
Two examples of screens from the Naming Speed© phonological training program

##### Phonics instruction training: BlendSeg

First, phoneme segmentation and blending skills are orally trained [127]. The task of phoneme blending into 10 words or pseudowords requires the child to blend orally several phonemes (e.g., */k/a/t/: cat*). The segmentation task is the reverse activity: 10 words or pseudowords are spoken and then segmented into phonemes by the child (e.g., *dog: /d/o/g/).* Second, the blended and segmented words and pseudowords are then read and written by the child. After copying them, the child is asked to write down the words she or he remembers.

#### Description of visual-attentional training

Similarly to phonological training, only the deficient processes identified in test 1 of Evadys© [117] and Sigl© [118] tests are trained. Visual-attentional cognitive deficits training (visual-attentional span and/or global/local analysis) is always associated with spelling memory training. The duration of the training of each visual-attentional process varies according to the nature and intensity of the disorders. For example, training may target visual-attentionnal span (Maeva©) and spelling memory (Lexi©) in the first month and global/local analysis (Switchipido©) and spelling memory (Lexi©) in the second month for children with two deficits.

##### Visual-attentional span training: *Maeva©*

 This program [128] is designed to increase the visual-attentional span, i.e. the number of visual elements to be processed simultaneously during ocular fixation. In these exercises, a sequence of two to seven visual stimuli including letters, pseudo-letters, numbers, geometric shapes or Japanese characters is briefly (420 to 120 ms) presented on the screen. When the sequence disappears, the child must perform a categorization task following six different instructions of increasing difficulty (e.g., Fig. 4). An algorithm adapts the difficulty of the exercise in real time, taking into account the child’s previous responses to keep the child’s success rate around 75%.

**Fig. 4 Fig4:**
[figure not shown]
Two examples of the Maeva© visual-attentional training program: (**a**) categorization with two families of stimuli, (**b**) categorization with all families of stimuli

##### Global vs. local analysis training: *Switchipido*©

This program, also computerized, is based on the Switchipido© software [66] which stimulates the visual-attentional switch between global and local levels of information processing. The display of hierarchical stimuli (large stimuli made of small drawings) allows a visual focus on the global shape and mobilizes the visual focus shift between the global and local levels (e.g., Fig. 5). The aim of these exercises is to reinforce the mechanisms of voluntary inhibition of details and the spontaneity in the global processing of complex visual stimuli.

**Fig. 5 Fig5:**
[figure not shown]
Two examples of the Switchipido© visual-attentional training program: (**a**) focus on the global level, (**b**) focus shift between the local and global level

##### Spelling memory training: *Lexi*©

This program, which is based on the principle of a mnemonic encoding/storage/retrieval process [129] consists of a “flash” reading of 20 semantically known words. After being read aloud by the child, the written words are presented again for a longer but limited time so that the child can copy them manually. After copying them, the child is asked to write down the words she or he remembers. The word lists are created by the speech-language therapist and adapted to each child according to his or her school level, spelling level and spelling regularity. In the phonological training, blending and segmentation is trained orally with 20 words or pseudowords. The same words are then read and written. In the visual-attentional training, the 20 words are also read and written. So, the amount of reading and spelling is similar in both training conditions.

#### Description of cross-modal process training

The phonological and visual-attentional training methods described above are based on either the auditory or non-simultaneous visual presentation of linguistic or non-linguistic units.

Cross-modal training is based on the simultaneous and repeated bimodal audio-visual presentation of linguistic units.

##### Grapho-phonemic integration training: GraphoGame©

The objective of this program is to reinforce the coupling of the orthographic code with the phonological code by reinforcing the specific cross-modal (i.e., audio-visual) link between letters and sounds. GraphoGame© software [74] is an audio-visual training program that simultaneously presents auditory and written stimuli for linguistic units of different sizes (phonemes, syllables, rhymes, words and sentences). This software, designed as a serious game, offers the child a game progression that becomes more and more complex. After listening to an oral stimulus, the child must click on the corresponding written presentation chosen from among several written stimuli (see Fig. 6). Twenty eight sequences are proposed, and each sequence offers 6 to 12 levels. If the success rate is less than 85%, the child must repeat the level.

**Fig. 6 Fig6:**
[figure not shown]
Four examples of the GraphoGame© cross modal training program. The child hears and chooses one of the proposed options: (**a**) the phoneme /c/, (**b**) the syllable /sat/, (**c**) the word “real”, (**d**) the child hears the word “week” and must put the letters in the right order

##### Reading fluency training: Accompanied, Repeated, Masked, Accelerated Reading (ARMAR)

This training consists in stimulating a child’s reading fluency and interest for reading [130, 131]. Each day, the child chooses a text from a book adapted to his/her reading level and must read the text in 6 steps. (1) The child reads the text aloud for 2 minutes. The parent notes the number of errors. (2) The parent reads the same text aloud at normal speed while the child follows the text that is read with a cursor (binary audio-visual processing). (3) Parent and child read aloud at the same time (accompanied reading) and the child follows the text with the cursor. (4) The child reads alone and again follows the text read aloud with the cursor; the parent corrects the wrong words or reads the words that are not read fast enough (repeated reading). (5) The child reads the text aloud alone, as quickly as possible, while listening to music of his or her choice with headphones (auditory masking). (6) The child reads the text aloud alone, as quickly as possible, without masked hearing. The parent notes the reading speed and the number of errors. The next day, a different text is read following the same steps.

### Criteria for discontinuing or modifying allocated interventions {11b}

The criteria for discontinuing or modifying allocated interventions are: (a) a serious adverse event (disease or pandemic) or environmental event (relocation), (b) withdrawal of consent, (c) cessation of daily training for more than 15 days without valid reason and subject to the judgment of the investigator, or an irregularity in daily training subject to the judgment of the investigator. Post-intervention measures for children that drop out from the intervention will be taken to perform an intention-to-treat analysis.

### Strategies to improve adherence to interventions {11c}

The recordings of the sessions carried out at home on the digital platforms of the various software programs that make up this protocol allow for precise control of the date, duration, frequency and scores of each training session. Weekly face-to-face visits with the speech-language therapist serve to longitudinally control compliance with the intervention. Protocol monitoring sheets indicating the number of sessions per week are filled out by the parents after each training session (see “parent sheets” in Additional files 2, 3, 4, 5).

### Relevant concomitant care permitted or prohibited during the trial {11d}

Weekly orthoptic and/or psychological care are not prohibited. Participation in another program of intensive care for a learning disability is a criterion for exclusion.

### Provisions for post-trial care {30}

This protocol is part of an ongoing speech and language therapy treatment. Its objective is to propose an intervention model that can be used in the treatment of a written word identification disorder. This type of evidence-based intervention is therefore a benefit for the patient who will be able to continue his or her care with the therapist who, in turn, will have strengthened his or her care practices after participating in this study.

### Outcomes {12}

The results of the study will be published 16 months after the last inclusion. Inclusions continue until September 2021.

### Participant timeline {13}

The schedule of enrolments, interventions and evaluations is presented in Table 1.

**Table 1 Tab1:**
[figure not shown]
Participant timeline

### Sample size {14}

In a pilot study on 20 patients with dyslexia, we determined that the effect size on reading efficiency between classical rehabilitation (baseline) and intensive rehabilitation was Cohen d = 0.867. Given that the literature on interventions for children and adolescents with reading disabilities gives effect sizes of 0.322 for phonological interventions (see [34]), expected effects on reading skills of a multimodal phonological, visual-attentional and cross-modal intervention should be greater. However, we preferred to be conservative and reduced the expected effect size to Cohen’s d = 0.700. Using G*Power 3.1.9.6, we found *n* = 55 per group. With an estimated drop-out rate of 10%, we will therefore include 120 participants.

### Recruitment {15}

The study is multicenter: 76 associate investigators have been recruited in France through the *Centre Référent des Troubles des Apprentissages* (CERTA) at the Nice-Lenval University Hospital Center and through professional training organizations. Each associate investigator may include a number of participants not defined in advance. If indeed associate investigators (i.e., speech and language therapists) include more than one patient, we will add the multi-level structure to the statistical data analyses. All the investigators recruited are state-qualified speech-language therapists and have expert practice in using these assessment and training methods.

## Assignment of interventions: allocation and blinding

### Allocation

### Sequence generation {16a}

Randomization is performed centrally at the Delegation for Clinical Research and Innovation of Nice (DRCI) of the Nice University Hospital Center by e-mail. Randomization is not stratified on the participating centers; the recruitment is competitive.

### Concealment mechanism {16b}

Randomization lists are produced using Query Advisor® v 7.0 software.

### Implementation {16c}

The DRCI assigns participants to interventions. The participant’s treatment group and inclusion number are then relayed to the investigator.

### Blinding

### Who will be blinded {17a}

Not applicable.

### Procedure for unblinding if needed {17b}

The clinical trial is open-label randomized since the intervention programs must be known by the investigators and the participants before the beginning of the experiment to ensure that the training runs smoothly.

## Data collection and management

### Plans for assessment and collection of outcomes {18a}

The assessment plan and all the data collected are entered in three Case Report Forms (CRFs) available online: The CRF Test 1 indicates the initial assessment plan and allows for baseline data collection. Group 1 and Group 2 CRFs indicate the assessment plans for each arm and allow for the collection of data in T2, T3, T4, T5 and T6 (see Additional files 6 and 7). Data quality is optimized by computerized assessments for all tests except for two leximetry tests (Alouette© and DeltaText©), a reading comprehension test (Orlec© L3), a spelling test (Chronosdictées©) and a self-esteem questionnaire. All the tests selected are referenced and scientifically validated (see Table 2).

**Table 2 Tab2:** An overview on the assessment batteries

Cognitive Processes		Measures	Labels
**Reading and spelling assessments**	Reading aloud	Meaningless texts reading	Alouette© /DeltaText©
		Meaningful texts reading	Evaléo©
		2 min word reading	Evaléo©: Eval2M
		Regular, irregular, pseudo-words reading	Evalec©
	Reading comprehension	Multiple choice statements	Orlec 3©
	Spelling	Phonetic, lexical and grammatical spelling	Chronosdictées©
**Underlying cognitive processes assessments**	Phonological process	Phonological analysis	Evalec©
		Phonological short-term memory	Evalec©
		Rapid automatized naming	Evalec©
		Categorical perception	RapDys©
	Visual-attentional process	Visual-attentional span	Evadys©
		Global/local analysis	Sigl©
**Complementary assessments**	Span memory	Digit span	Evaléo©
		Visual-spatial span	Corsi©
	Reading disability impact	Reading motivation, academic performance and self-esteem	Likert scales
	Oral language	Vocabulary and syntactic comprehension	Evaléo©
	Matrix Reasoning	Fluent and visual-spatial intelligence	Wisc 5©

#### Word identification assessment

##### Meaningless texts

*Alouette*© [113, 114]: This test (265 words) which is considered the gold standard of leximetry tests assesses speed and accuracy when reading a meaningless text. This test provides a reading age [113], a speed score, a precision score, a precision index and a speed index [114]. The text includes trick questions for readers who tend to massively use contextual anticipations (“*poisson*” instead of “*poison*” after “*lac*”) or identification behaviors (items that are visually or phonologically close, such as “*amie / annie*” or “*gai / geai*”). The text is surrounded by drawings that induce contextual errors (drawing of a “*écureuil*” near the word “*écueil*”). Time limit for reading is 3 minutes. 

*DeltaText©* [119, 123]: Four different meaningless texts whose words (*n* = 201 words) are balanced in length, lexical frequency, and syllabic and phonemic complexity are proposed to limit a possible test/re-test effect. All words are regular to allow reading even if the spelling lexicon is insufficient. Time limit for reading is 3 minutes. The number of errors and the reading time are recorded.

##### Meaningful texts

*Evaléo*©, *Mouette/Pingouin* [115]: These two meaningful texts (*n* = 450 words) are balanced in word and sentence length, lexical frequency and syllabic and phonemic complexity in order to limit a re-test effect. Reading time and accuracy are recorded. Time limit for reading is 3 minutes.

##### Identification of written words

*Evaléo*©, *Eval2M* [115]: This test (*n* = 263 words) assesses the percentage of words read correctly in a limited time of 2 minutes. Words are presented in 10 columns and according to length and frequency. 

*Evalec©* [116]: This test assesses reading of regular words, irregular words and pseudo-words. This computerized test presents the words to be identified one by one on the screen. The particularity of this test is to use voice detection to measure the time needed to correctly read the words. The lexical or sublexical reading processes are assessed by calculating the latency time in ms when correctly reading items and the percentage of errors when reading regular words (*n* = 36), pseudo-words (n = 36) and irregular words (n = 36). The length effect is assessed by comparing the accuracy and speed measures for short and long irregular words (*n* = 20) with those for short and long pseudowords (n = 20).

#### Reading comprehension assessment

The *ORLEC L3©* [121, 122] assesses word decoding speed and sentence comprehension. This closure test presents sentences to be completed (n = 36) with a word selected among 5 proposed words. The raw score corresponds to the number of correct items completed in 5 minutes.

#### Spelling assessment

*Chronosdictées*© [120] assesses lexical, morphosyntactic and phonetic spelling. Two dictations, A and B, of sentences are used for each grade level in elementary and middle school. The results are expressed in number of errors: 3 scores for the number of phonetic, lexical and grammatical errors, 2 scores for segmentation errors and omissions of words and a score for the total number of errors.

#### Assessment of underlying cognitive processes

##### Categorical perception assessment

Allophonic discrimination skills are assessed by syllable identification and discrimination tasks (/də/ and /tə/) using RapDys© software [123]. The tasks consist in discriminating and identifying increasingly fine acoustic differences between two different phonemes. The Voice Onset Time (VOT) changes from allophonic peaks at +/− 75 ms VOT to phonemic peaks at +/− 5 ms VOT.

##### Phonological processes assessment

For the following tests, Evalec© software calculates a score for precision and for speed [116].The pseudoword repetition task assesses phonological short-term memory and is composed of pseudowords (*n* = 12) with a simple syllabic structure and pseudowords (*n* = 12) with a complex syllabic structure, both with 3 to 6 syllables.The task of deleting the first syllable of trisyllabic pseudowords (*n* = 10) assesses the phonological analysis (e.g., povidu/vidu). The two tasks of deleting the first phoneme of monosyllabic pseudowords (*n* = 24) assess the phonemic analysis (e.g., puf/uf and pra/ra).The color-naming task assesses rapid automatized naming. A matrix of color images (*n* = 54) and a matrix of written color names (*n* = 54) are presented in 9 lines of 6 colors in random order. Three color names have a CVC syllabic structure *(rouge, jaune, vert)* and three have a CCV syllabic structure *(bleu, blanc, gris).*

##### Visual-attentional processes assessment

Visual-attentional span is measured by global and partial letter report tasks with Evadys© software [117]. In the Global Report condition, the participant must name a sequence of five consonants presented for 200 ms. In the Partial Report condition, a vertical bar appears and indicates the position of the letter to be named among the five letters presented for 200 ms. The letter sequences are formed so as not to activate any memorized lexical knowledge and so as to minimize crowding. Beforehand, an isolated letter identification task is presented in order to control for single letter processing speed. The software calculates a score based on the number of successful sequences and a letter span. 

Sigl© software [118] assesses the ability to focus attention on a global or local mode of analysis of visual information. The stimuli are drawings of hierarchical objects presented for 175 ms for which a global or local level is selected as per the instruction of a target. The software calculates the difference in performance between Control and Interference conditions to assess the local and global interference in response time and percentage of errors. To calculate the asymmetry of the interference, the local interference effect is subtracted from the global interference effect and this difference is typically positive.

#### Span memory assessment

Assessment of the digit span with Evaléo© software [115]: Repetition of a series of 2 to 7 digits in forward (short-term memory) and backward (working memory) order assesses verbal memory. The number of digits correctly repeated determines the digit span.

Assessment of the visual-spatial span [132]: The Corsi block test consists in reproducing, in the same or reverse order, the sequence in which the clinician points to different cubes. The number of cubes in the sequence gradually increases, thus determining the visual-spatial span.

#### Assessment of reading disability impact

Changes in reading disability, reading motivation, academic performance and self-esteem are measured by two questionnaires. These questionnaires consist of several statements for which the respondent expresses his or her degree of agreement or disagreement. Two Likert scales are constructed, one for the child, one for the parents, and are proposed before and after training (for more details, see Additional file 8).

#### Optional assessment

If the participant did not have an oral language assessment prior to inclusion, three measures will be taken to assess vocabulary expression, lexical syntactic comprehension. Naming Vocabulary test [115] assesses the lexical stock of known words produced and naming time. The picture/word association [115] assesses the lexical stock. The picture/sentence association [133] assesses syntax understanding in sentences.

If the participant has not had an assessment of intellectual efficiency, the *Matrix Reasoning* test from the Wechsler Intelligence Scale for Children, Wisc-5 [134], is administered to determine an index of fluid and visual-spatial intelligence [135].

### Plans to promote participant retention and complete follow-up {18b}

The principles of therapeutic education and shared decision making are used to maintain the children’s participation during the 16 months. Participants and their parents receive all the information necessary to understand developmental dyslexia and the protocol of care offered to them. This information is presented and repeated throughout the duration of the study on different media (slide show and fact sheets). Most interventions at home are standardized and computerized. The role of the parents is making sure that the children respect the daily sessions, supporting them by being present during the numerical training and carrying out the verbal trainings such as BlendSeg or ARMAR. The children and their parents are also trained in using the software on their own by means of tutorials. The outcomes obtained during the different phases of the study are communicated very precisely and explained to the parents and children. The child can decide to leave the study at any time. The data collected until the withdrawal of consent or the end of participation is kept and analyzed as specified in the information leaflet given to the parents.

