**Discussion:**

The main objective of this study is to assess whether the three types of intensive intervention (phase 2) improve reading skills compared to baseline (i.e., non-intensive intervention, phase 1). The secondary objectives are to evaluate the effectiveness of each intervention and to test the effects of order of delivery on reading intervention outcomes. Reading comprehension, spelling performance and reading disorder impact of dyslexic readers are assessed immediately before and after the multimodal intervention and 2 months post-intervention.

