#### Secondary evaluation criteria

Related to the secondary objectives:Reading efficiency after the phonology training and after visual-attentional training will be measured by the five reading tests in Test 3 for the two groups (G1: PHO/VA/CM, G2: VA/PHO/CM).Reading efficiency after the two phonological and visual-attentional training periods conducted in a different chronological order in each group, will be measured by the five reading tests in T4 for the two groups.Spelling skills will be measured by Chronosdictées© [120] which proposes two versions with sentences matched in length, lexical frequency and phonetic complexity.Reading comprehension will be measured by the closure test ORLEC L3© [121, 122].Reading disorder impact (reading interest, academic performance and self-esteem) will be measured by two questionnaires completed by each child and his or her parents, in which they express their degree of agreement or disagreement.

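### Families are told the outcome results during the trial and then rate self-esteem, academic performance and reading interest themselves, so a T2 to T5 change in these secondary ratings may partly reflect the feedback

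*Protocol article*

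**What the plan says.** Under Plans to promote participant retention and complete follow-up {18b}, the protocol article says: "The outcomes obtained during the different phases of the study are communicated very precisely and explained to the parents and children". The aim of that section is retention over the whole trial: "The principles of therapeutic education and shared decision making are used to maintain the children’s participation during the 16 months".

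The people who receive this feedback also supply one of the secondary outcomes. Under Secondary evaluation criteria, reading interest, academic performance and self-esteem "will be measured by two questionnaires completed by each child and his or her parents". The section Assessment of reading disability impact adds: "Two Likert scales are constructed, one for the child, one for the parents, and are proposed before and after training". The abstract says that reading disorder impact, with comprehension and spelling, is among the measures that "are assessed immediately before and after the multimodal intervention and 2 months post-intervention".

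Hypothesis 2 (Secondary hypotheses) sets these ratings at test 5 against test 2. The trial has no untrained control group (Trial design {8}), and nobody is blinded: "The clinical trial is open-label randomized since the intervention programs must be known by the investigators and the participants".

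**The concern.** A child and parents who have been told exactly how the reading scores moved, and are then asked about self-esteem and school performance, may answer partly from what they were told. A rise could follow news of a gain, and a fall could follow news of no gain. Neither would be a direct effect of training on how the child feels or performs.

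At stake is the interpretation of Hypothesis 2 and of the secondary objective on reading interest, academic performance and self-esteem. The contrast is within child, and both randomized groups are described as receiving the same feedback, so randomization does not remove the effect.

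**Working it through.** The article gives no figure for feedback or its effect, so there is none to reproduce. The check reads the sections together, counts feedback rounds, and adds one illustration on assumed values.

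**1. When feedback is given.** Section {18b} does not date it. Feedback given only after T6 could not help keep children in for 16 months, so the natural reading is disclosure while testing continues. No section holds results back until the questionnaires are completed.

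**2. Whether a control change exists for the ratings.** The abstract places the ratings just before the intervention, just after it and 2 months later. The section Statistical analysis compares later gains with the T1-T2 gain, but names reading, spelling and comprehension scores as the dependent variables. Its item on the questionnaires describes composite scores, or failing that histograms and chi-square tests, with no subtraction of a phase 1 change. The text shown therefore states no T1-T2 rating change to set against T2-T5.

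**3. Rounds of feedback per interval**, assuming results are given after every test:

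| Interval | Results given within it | Rounds | 8-week blocks |
|---|---|---|---|
| T1-T2 | T1 | 1 | 1 |
| T2-T5 | T2, T3, T4 | 3 | 3 |

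That is one round per block throughout, but three in total across the interval used for Hypothesis 2.

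**4. What visit order changes.** If questionnaires come first at both visits, the T2 rating follows 1 round and the T5 rating follows 4, a difference of 4 − 1 = 3. If results come first at both, it is 5 − 2 = 3. If the order differs between visits, it ranges from 4 − 2 = 2 to 5 − 1 = 4. Fixing the order therefore keeps the difference at 3. Putting the questionnaires first also means that no one rates just after hearing the T5 result.

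**5. Illustration of size.** The shifts are assumed and do not come from the article. Let feedback alone move a rating by δ, in SDs of the within-child change, and use a paired two-sided 5% t-test as a stand-in analysis. The noncentrality is δ√n. With n = 110 (2 × 55, the sample-size figure), √110 = 10.488 and the critical value is about 1.98. The last column uses n = 120, all children included.

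| δ | δ√110 | Significant, n = 110 | Significant, n = 120 |
|---|---|---|---|
| 0.05 | 0.524 | 8% | 8% |
| 0.1 | 1.049 | 18% | 19% |
| 0.2 | 2.098 | 55% | 58% |
| 0.3 | 3.146 | 88% | 90% |

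A modest shift could be enough for a significant result with no training effect on the ratings. The table does not show that such a shift occurs.

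**The case against.** The strongest reply is that the article fixes neither the timing nor the content of the feedback. Visit order may be set in the case report forms, the participant timeline or the questionnaire supplement, none of which is shown. That stands, and it is why this is a risk and not a demonstrated bias.

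Second, an open-label trial without an untrained control limits these ratings with or without feedback. Parents also see progress directly: in the ARMAR reading exercise they note speed and errors each day. This stands too. Controlling formal feedback reduces the problem but does not remove it.

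Third, the trial sits within ongoing therapy, and its retention plan rests on shared decision making. Withholding a child's scores until T6 would conflict with that. This is a fair objection to a full embargo, but not to asking for the questionnaires first.

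A reader might go further and infer any of the following. The article does not support them:

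- **The main reading contrast is biased.** The main criteria are timed and error-scored. Feedback might affect motivation, but no bias is shown.
- **Feedback teaches the Alouette items.** The article does say of that test: "The text includes trick questions for readers who tend to massively use contextual anticipations". But {18b} speaks of outcomes, not of item errors, and Data management {19} lists error counts or percentages, times, percentiles and standard deviations. Retest gain on a single text is a separate matter that exists without feedback.
- **Exposure is unbalanced four to one.** That compares cumulative rounds before T5 with those before T2. Within the intervals it is three against one.
- **The baseline phase is free of feedback.** Results given after T1 fall inside it.

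**Conclusion.** The point holds for the child and parent ratings of reading interest, academic performance and self-esteem, and only for those. The raters are unblinded and are told the outcome results. The T5 against T2 contrast has neither an untrained control nor a stated phase 1 rating change, so a feedback effect cannot be separated from a training effect.

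The size is unknown. The count of one round in T1-T2 and three in T2-T5 assumes feedback after every test, and the percentages rest on assumed shifts. The direction is not fixed either, since feedback could raise or lower a rating. The comparison of PHO/VA with VA/PHO order is little affected, because feedback is described alike for both groups. No sample-size figure changes.

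**What to change.** In Assessment of reading disability impact and in section {18b}, add that:

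1. at each visit where the questionnaires are given, the child and parents complete them before any test result from that visit is discussed;
2. feedback during the trial is limited to summary scores, with no item-level errors. Item teaching is not shown, but the present wording sets no limit on content.

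Because families will still know the results of earlier rounds, also state that the Hypothesis 2 ratings are open-label and may include a feedback effect. For visits already completed, report when results were given relative to the questionnaires, where this is known.

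The cost is a minor constraint on visit order and less detailed feedback for families. Holding all scores until T6 is optional: it would reduce the feedback effect further, but it trades off against shared decision making and retention.
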